**Research Protocol**

Synopsis

This pragmatic trial with cluster randomization of AEDs is designed to evaluate the effectiveness and cost-effectiveness of screening methods (modified PAT vs FAST vs modified SASQ) and interventions (Leaflet vs Brief advice vs Brief counselling) in routine AED care. Due to the design implications of a multi-level factorial design in AEDs the proposed trial involves a universal screening approach in which relevant data for a sub-sample of linked presentation population is collected. Therefore, the trial design encompasses a 3x3 factorial trial, screening method (modified PAT vs FAST vs modified SASQ) and intervention (Leaflet vs Brief advice vs Brief lifestyle counselling). The main advantages of utilising a factorial approach are twofold. First each of the three elements (screening tool and intervention) can be analysed independently with sufficient power to make meaningful interpretation of relative effectiveness. Second, the method enables meaningful interpretations of the relative effectiveness of any combination of screening method and intervention. Because the universal screening population encompasses a sub-group of linked presentation targeted population we can make meaningful comparisons of the relative effectiveness and interactions associated with screening approach in AEDs. Nine AEDs across the North East, London and the South East Regions of England will be recruited. AEDs will be randomly allocated to one of three intervention conditions: the patient information leaflet control condition (n=3), the structured brief advice condition (n=3); and lifestyle counselling by an Alcohol Health Worker (n=3). To test the relative effectiveness of different screening methods all AEDs will be randomised to either a modified single item screen (Single Alcohol Screening Question; M-SASQ) or a modified Paddington Alcohol Test (SIPS-PAT) or FAST Alcohol Screening Test (FAST) screening method. AEDs in the modified PAT condition will use targeted screening as per the standard PAT protocol. AEDs in the FAST and modified SASQ conditions will use universal screening for case identification and collect information about whether a patient would be part of a linked presentation group and then use statistical simulation to analyse any interactions. Screening randomisation will be stratified by median AED admission rates (2 levels) and intervention condition (3 levels). Each AED will recruit a minimum of 131 patients who are hazardous or harmful drinkers into the trial and a short baseline assessment will be carried out. Outcome will be assessed at 6, and 12 months after intervention. Outcomes will include system implementation outcomes and patient outcomes. We will also examine the practitioner and organisational factors associated with successful implementation.

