
Study aim

To evaluate the implementation, effectiveness and cost effectiveness of BI delivered by an alcohol health worker aimed at reducing excessive drinking in routine AED care compared to brief advice and a patient information leaflet (PIL) in hazardous and harmful drinkers identified by universal or targeted screening.

Study objectives

- To conduct a pragmatic multicentre cluster randomised controlled trial of screening and brief interventions for hazardous and harmful drinkers in AEDs in three English regions.
- To compare the effectiveness and cost effectiveness of brief advice conducted by AED staff (including dedicated AHWs) (Tier 1) with referral to an alcohol health worker (Tier 2) of patients with hazardous and harmful alcohol consumption identified by targeted opportunistic or universal screening.
- To assess the relative impact of the three implementation strategies on alcohol screening and brief intervention activity in AEDs.
- To identify the attitudinal, practical, skill, resource, and reinforcing factors that predict successful implementation of screening and brief intervention in AEDs.
- To identify the optimal method of alcohol screening in AED.
- To assess the relative impact of the three implementation strategies on uptake of alcohol services, including an alcohol helpline.

Hypotheses

- Brief Lifestyle Counselling intervention by an alcohol health worker for hazardous and harmful drinkers identified by targeted screening is more effective and cost effective than Brief Advice conducted by AED staff (including dedicated AHWs) in the typical AED setting.
- Brief Lifestyle Counselling intervention by and alcohol health worker and Brief Advice by AED staff (including dedicated AHWs) are more effective and cost effective than an information leaflet alone.
- Access to referral to an alcohol health worker results in greater screening and intervention activity than training of AED staff in screening and brief intervention alone.
- Attitudinal, practical, skill, resource, and reinforcing factors predict screening and intervention activity.
- Briefer screening methods result in greater implementation of screening activity than more complex methods.

Setting

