The AED study design differs from the PHC study in not having targeted versus universal screening as a separate factor in the design. There are two main reasons for this. First, we have looked closely at the potential of a factorial design including universal versus targeted screening. However, the number of AEDs that would be required to have a separate screening factors (minimum n=18) would exceed the likely number of AEDs agreeing to participate in the there regions (based on previous experience from our national AED survey (Drummond et al., 2003)). Second the PAT has been designed as a targeted screening method in the context of routine AED assessment. The FAST and SASQ on the other hand have been designed as universal screening tools. Therefore we propose that universal versus targeted screening be studied in two ways within this trial. First we will randomize AEDs to targeted screening with the modified PAT and universal screening with FAST or the modified SASQ, which is appropriate to the design of the instruments. Second we will record the patients’ presenting clinical conditions and demographic factors in the universal screening arms of the study to identify which factors are most strongly associated with alcohol positive cases. Together these findings will allow the comparison of targeted and universal screening and lead to the development of clinical guidelines for AEDs on the most efficient form of targeted screening approach.

Table **1**. Overall AED study design.

| Intervention condition **>** | Leaflet by AED staff | Brief advice by AED staff | Brief Lifestyle  Counselling intervention | Totals |
| --- | --- | --- | --- | --- |
| Screening condition V |
| FAST Alcohol Screening Test | AED n=1;  Patients n=131 | AED n=1;  Patients n=131 | AED n=1;  Patients n=131 | AED n=3;  Patients n=393 |
| Modified Single Alcohol Screening Question | AED n=1;  Patients n=131 | AED n=1;  Patients n=131 | AED n=1;  Patients n=131 | AED n=3;  Patients n=393 |
| SIPS Paddington Alcohol Test | AED n=1;  Patients n=131 | AED n=1;  Patients n=131 | AED n=1;  Patients n=131 | AED n=3;  Patients n=393 |
| Total per intervention | AED n=3  Patients n=393 | AED n=3  Patients n=393 | AED n=3  Patients n=393 | AED n=9  Patients n=1179 |

Screening conditions

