3. *Brief Lifestyle condition:* This is based on the St Mary’s Hospital model. AED staff (including dedicated AHWs) will be trained to carry out universal alcohol screening and to refer hazardous and harmful drinkers identified by screening to an Alcohol Health Worker (AHW), by making an appointment usually the following day or as soon as possible after AED attendance. Before leaving the AED the patients in this condition will be given a PIL and Simple structured advice as above. The AHW will be experienced in carrying out alcohol assessment and brief interventions. The AHW will carry out a brief lifestyle counseling intervention lasting for 20 minutes using the modified Drink-Less brief intervention materials (level 2).

AED recruitment

Eligible AEDs in the participating regions will be contacted initially by phone and mail to canvass participation in the study. We will use contacts previously made in our national survey of AEDs (Drummond et al., 2003) and through the BAEM with [name] assistance. Thereafter site visits will be made by the research team to explain the trial protocol, secure clinician consent to participate in the study and to organize training.

Training and support

All participating AEDs will be provided with training and support appropriate to the allocated condition in the study. In the control condition staff will be trained by experienced SBI clinical trainers to carry out screening, feedback and provide a PIL. A member of the research team and a specialist clinician will provide ongoing support in implementing the research and clinical procedures.

In the Brief Advice condition training and support will be provided by a specialist clinician (Alcohol Health Worker) who will act as clinical coordinator for the study, and a member of the research team. Training will be carried out by experienced trainers for medical, nursing and administrative staff in seminars and individual training (see ‘incentives’ below). Trainers will be Alcohol Health workers recruited from local alcohol agencies. Each AED will have an allocated clinical coordinator who will champion screening and brief intervention and provide ongoing support and supervision for AED staff, including an AED staff support group. The research coordinator will provide support on implementation of the research procedures.

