The sample size calculation is designed to account primarily for intervention level outcomes. Powering the study in this way will also account statistically for appropriate outcomes for screening approach and screening method. The primary outcome for this study is the proportion of patients who consume alcohol within recommended levels at 6 month follow up. Recent meta-analysis (Moyer et al 2002) suggest that the difference between brief intervention and control is of the order 13%, 5% reduction in the control group and 18% in the brief intervention group. In order to detect a difference of this magnitude at the 5% significance level with 80% power, for a 2-sided test, requires 109 patients in each of the 3 groups, a total of 327. Our experience with other multi-centre randomized controlled trials of interventions for alcohol use disorders suggests that with assiduous follow-up the potential loss to follow-up across groups is of the order 25%. Taking this loss into accounts inflates the sample required to 131 in each group, a total of 393 patients per intervention.

The proposed study involves a cluster design and requires a statistical adjustment to account for any potential cluster effect. The literature, and our previous experience of trials in primary care, suggest an intra-class correlation coefficient of 0.04 is appropriate. Assuming a cluster size of the order 131 patients this inflates the sample size calculation by a factor of 2.7 requiring patients 393 in each group, a total of 1179, with an expectation that at least 882 will be followed up at 6 months.

We propose to recruit 9 AED’s. AED populations will be screened using 1 of 3 screening method groups (3 AED’s in each group) and will receive 1 of 3 intervention (3 AED’s in each group).

Planned analysis

As the study is pragmatic in design, the planned analysis will be by intention to treat. The primary outcome is dichotomous in nature, drinking within or above recommended levels, and will be analysed logistic regression adjusting for all known prognostic factors, data will be presented as odds ratios and their corresponding confidence intervals. Secondary analyses will be undertaken using the appropriate method for the outcomes, controlling where appropriate for intake values and other known prognostic variables using analysis of covariance. Simulations will be undertaken to encompass both screening approach groups and intention to treat analysis will be undertaken on both groups.

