Due to the nested factorial nature of the study, we will use multi-level modelling to explore potential interactions between each of the levels nested within the trial.

Practice and patient factors will be utilised as part of regression model to explore possible prognostic factors that impact on outcome. Interaction analysis will explore any possible interactions between practice and patient characteristics and outcome. The efficacy of the interventions will be explored with a secondary analysis utilising a per protocol approach. A sub-group of the trial population, those who engaged in the allocated treatment will be utilised for this analysis.

Ethical and Research Governance Approval

We will seek Multi-centre ethical approval for the trial plus local agreement from all relevant LRECS. In addition, research governance approval will be sought from all relevant acute NHS trusts.

Project Timescales and Funding

The trial duration will be 2 years beginning at the point that ethics and governance approval has been secured.

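### With one AED per screening-by-intervention cell, combinations can be compared only by assuming additive effects, so the combination and interaction claims and the wording of hypothesis 1 go beyond the design

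*Protocol*

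**What the plan says.** The Synopsis states that "the trial design encompasses a 3x3 factorial trial", with the AED as the unit of randomisation. It lists as a main advantage that "the method enables meaningful interpretations of the relative effectiveness of any combination of screening method and intervention", and it expects meaningful statements about interactions with screening approach.

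Design, Table 1, shows one AED and 131 patients in every cell, for example "FAST Alcohol Screening Test | AED n=1". Sample size calculation confirms the total: "We propose to recruit 9 AED’s", three per screening method and three per intervention. Planned analysis adds that "we will use multi-level modelling to explore potential interactions between each of the levels nested within the trial", and separately mentions interactions of practice and patient characteristics with outcome.

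Hypothesis 1 concerns lifestyle counselling "for hazardous and harmful drinkers identified by targeted screening is more effective and cost effective than Brief Advice". According to the Synopsis and Design, only the modified PAT (SIPS-PAT) AEDs use targeted screening. The study aim and second objective cover patients found by either approach. The description of the brief lifestyle condition says "AED staff (including dedicated AHWs) will be trained to carry out universal alcohol screening and to refer hazardous and harmful drinkers".

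**The concern.** A cell comparison that does not lean on the other cells sets one hospital against another. Any difference could come from the screening tool and intervention together, or from case mix, staffing or follow-up at those two hospitals. More patients per AED do not help, because what is missing is a second hospital in the cell.

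A recommendation of a best combination for AED practice could therefore reflect which hospital fell in which cell. The same applies to hypothesis 1 as worded. Only one AED combines SIPS-PAT with counselling and only one combines it with brief advice.

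**Working it through.** **Inputs from the protocol.** Nine AEDs, one per cell (Table 1). From Sample size calculation: 131 patients per AED, 25% loss (131 × 0.75 = 98.25, taken as 98 followed up), ICC 0.04, target 5% versus 18% (13 points), two-sided 5% level, 80% power. The ICC is said to come from the literature and from primary care trials, so 0.01 and 0.02 are added here as assumptions.

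**The plan's own figure.** The two-proportion formula with continuity correction gives 109 per group for 5% versus 18%, as stated (94 without the correction). This figure compares interventions; no calculation addresses cells or interactions.

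**Degrees of freedom at AED level.**
- Additive model: 1 + 2 + 2 = 5 parameters, leaving 9 − 5 = 4. Adjusting also for the two-level admission-rate stratifier leaves 3.
- With the interaction: 5 + (2 × 2) = 9 parameters, leaving 9 − 9 = 0.

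In the second model the nine fitted cell means reproduce the nine AEDs, so nothing is left from which to estimate variation between AEDs. A random AED intercept does not rescue it. The likelihood is already at its maximum with that variance at zero, so the fitted model's interaction test becomes the patient-level one.

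**One AED against one AED, no true difference.** The design effect is DE = 1 + (98 − 1) × ICC. The SD of the observed difference is √[2p(1 − p) × DE / 98]. The type I error of a test that ignores clustering is approximately 2[1 − Φ(1.96/√DE)].

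| ICC | DE | SD, p = 5% | SD, p = 18% | Type I error, formula | Type I error, simulation (p = 5-18%) |
| --- | --- | --- | --- | --- | --- |
| 0.01 | 1.97 | 4.4 points | 7.7 points | 16% | about 15-17% |
| 0.02 | 2.94 | 5.3 points | 9.4 points | 25% | about 23-26% |
| 0.04 | 4.88 | 6.9 points | 12.1 points | 37.5% | about 33-38% |

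At ICC 0.04 each AED is worth 98/4.88 ≈ 20 independent patients. Power for 5% versus 18% between two single AEDs is then about 25%, even if the ICC were known exactly.

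**Patient-level interaction test (4 df), no true interaction.** Beta-binomial simulation with 98 per AED gives rejection in about 70-75% of trials at ICC 0.04, 52-55% at 0.02 and 29-33% at 0.01. The spread reflects the true proportion (5-18%) and the choice of test statistic.

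**Hypothesis 1 against the rest of the protocol.** The restriction to targeted screening leaves one SIPS-PAT AED giving counselling and one giving brief advice. If the restriction is read as applying only to the counselling side, that side is still a single hospital. The study aim, the second objective and the sample size, with three AEDs per intervention, are all broader.

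**The case against.** Five points can be made for the protocol.

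- **Planned analysis never writes down a saturated screening-by-intervention model.** It calls the interaction work exploratory and names patient characteristics. This stands in part. Interactions with patient-level characteristics vary within AEDs and can be estimated. A reader might infer that the whole planned interaction analysis is unidentifiable, but the text does not support that. The problem covers screening by intervention.
- **Under an additive model every combination does have an estimate.** This is true, but the Synopsis does not state the assumption, and the design cannot test it.
- **Hypothesis 1 has a wider route.** Linked-presentation status is recorded in the FAST and modified SASQ AEDs, so such patients from all nine AEDs could contribute. A reader might infer that no analysis can address hypothesis 1, and that would be too strong. The route still needs additivity, because those patients are found with another tool under universal screening. The planned statistical simulation adds no hospitals.
- **The rejection rates depend on the ICC.** They do, and they are far smaller at 0.01, but even then they are three times the nominal 5% or more.
- **The number of AEDs was limited, and the protocol says so.** Design rejects a separate targeted-versus-universal factor because it would need at least 18 AEDs. That number matches 3 × 3 × 2 with one AED per cell, so it does not address replication within cells.

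**Conclusion.** The claims about combinations and about interaction with screening approach are not supported by a design with one AED per cell. Nor is the multi-level interaction modelling so far as it covers screening by intervention. The aliasing follows from Table 1 alone and needs no assumption about the ICC. The error rates do need one. At the protocol's 0.04, chance differences between two hospitals have an SD of about 7-12 points against a 13-point target; at 0.01 the SD is about 4-8 points. These figures assume 98 followed up per AED and true proportions of 5-18%.

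Hypothesis 1 as worded rests directly on one hospital against one and is out of line with the aim, the second objective and the sample size.

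A reader might infer that the primary intervention comparison fails too. The documents do not support that on this ground: it has three AEDs per arm and 4 residual degrees of freedom in the additive model. Whether it is adequately powered is a separate question. The point should be fixed, but it does not undermine the primary comparison.

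**What to change.** 1. In the Synopsis, replace the combination and interaction claims with a statement that combinations can be compared only by assuming additive screening and intervention effects, and that this design cannot test that assumption.
2. In Planned analysis, use the additive intervention-plus-screening model for AED-level inference, with 4 residual AED degrees of freedom (3 if the admission-rate stratifier is included). Report the nine cells descriptively, labelled as confounded with hospital. Keep exploratory interactions with patient-level characteristics.
3. Restate hypothesis 1 for all enrolled hazardous and harmful drinkers, in line with the study aim. Add a supporting analysis in linked-presentation patients from all nine AEDs that states its additivity assumption.
4. Separately, reconcile the universal-screening wording in the brief lifestyle condition with the SIPS-PAT allocation of one AED in that arm.

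This costs wording in the protocol and any analysis plan, and no extra data. What is lost is confirmatory testing of the interaction and of a best combination. Keeping those would need replicated cells: two AEDs per cell, 18 in all, would leave 18 − 9 = 9 residual degrees of freedom in the saturated model. The protocol considers that number of AEDs out of reach.

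### The randomised targeted-versus-universal contrast cannot be separated from the screening tool, yet the protocol counts it as evidence on screening approach and says the sample size covers it

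*Protocol*

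**What the plan says.** The Synopsis ties approach to tool. For SIPS-PAT: "AEDs in the modified PAT condition will use targeted screening as per the standard PAT protocol". For the other two tools: "AEDs in the FAST and modified SASQ conditions will use universal screening for case identification". Table 1 gives each tool three AEDs, one per intervention condition.

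The Design section explains that approach is not a factor of its own, because that would need at least 18 AEDs. It then offers two ways to study approach within the trial. The first is randomised: "First we will randomize AEDs to targeted screening with the modified PAT and universal screening with FAST or the modified SASQ". The second records presenting conditions and demographics in the universal arms "to identify which factors are most strongly associated with alcohol positive cases". It concludes: "Together these findings will allow the comparison of targeted and universal screening".

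The Synopsis adds that FAST and M-SASQ AEDs will "collect information about whether a patient would be part of a linked presentation group and then use statistical simulation to analyse any interactions". Because the universal population contains the linked-presentation group, it says, "we can make meaningful comparisons of the relative effectiveness and interactions associated with screening approach in AEDs". Planned analysis states: "Simulations will be undertaken to encompass both screening approach groups and intention to treat analysis will be undertaken on both groups". Sample size calculation says that powering for the intervention also takes care of outcomes for screening approach and screening method.

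**The concern.** If approach and tool never vary independently, the randomised contrast has one answer to two questions. The System measures section compares screening, conversion and intervention rates across the three tools. A gap between SIPS-PAT and the rest in any of these could be reported as evidence for targeting when it comes from the questions asked, or the reverse. The Design section intends guidance for AEDs on targeted screening to follow from this work, so the label put on the result matters.

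There is a second issue for patient outcomes. The intention-to-treat analysis is to be run on two approach groups. Read with the Synopsis, one of these is a part of the other. Two intervention effects from such groups, set side by side, are not a test of whether the effect differs by approach.

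**Working it through.** **1. The plan's sample size, and what it contains.** Inputs from Sample size calculation: 5% v 18%, two-sided 5%, 80% power. Without continuity correction:

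n = [1.960·√(2·0.115·0.885) + 0.842·√(0.05·0.95 + 0.18·0.82)]² / 0.13² = (0.884 + 0.372)² / 0.0169 = 93.3, so 94.

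With continuity correction: (93.3/4)·[1 + √(1 + 4/(93.3·0.13))]² = 108.2, so 109. The stated 109 reproduces. The only other inputs are loss to follow-up and an intra-class correlation. Nothing in the calculation refers to an approach effect, a linked-presentation share or a 3 v 6 split of AEDs.

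**2. Aliasing in the nine AEDs.**

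| Tool | Targeted AEDs | Universal AEDs |
|---|---|---|
| SIPS-PAT | 3 | 0 |
| FAST | 0 | 3 |
| M-SASQ | 0 | 3 |

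- The targeted indicator equals the SIPS-PAT indicator (correlation 1.0).
- Intercept, two tool terms and two intervention terms: rank 5 for 5 columns.
- Add the approach column: still rank 5, now for 6 columns. Approach is not estimable.
- Cross approach with tool and intervention in the 18 AEDs that the Design section names: rank 6 for 6 columns. Approach becomes estimable.

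The rank depends on the AED layout, so no number of patients in these nine AEDs changes it.

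**3. What this means for a result.** The documents give no linked-presentation share or positivity rates, so these are assumptions. Suppose 30% of attenders are linked, 50% of those screen positive, 20% of the others do, and all tools are equally accurate. Conversion is 50% under targeting and 0.3·50% + 0.7·20% = 29% under universal screening, all due to who is screened. Now suppose that linked status is irrelevant and that SIPS-PAT flags 50% of anyone screened where the other tools flag 29%. The observed rates are the same, all due to the tool. The randomised contrast cannot tell these cases apart.

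**4. What the universal AEDs can show.** Here the tool is fixed. Under the first set of assumptions, screening linked presentations only would screen 30% of attenders and find 0.3·50% = 15 of the 29 positives per 100 attenders, that is 52%. This is a useful yield comparison. It is not randomised, and it comes from AEDs that ran universal screening, so it says nothing about how staff would take up targeted screening in operation.

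**5. Two analyses of nested groups.** Let f be the linked share among the patients analysed, assumed equal across arms. On the risk-difference scale, whole-group effect = f·(linked effect) + (1−f)·(non-linked effect). Hence

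whole − linked = (1−f)·(non-linked − linked).

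With f not given and taken as 0.2 to 0.8, the gap between the two results is 80% down to 20% of the real difference in intervention effect. The two estimates share patients (correlation √f, 0.45 to 0.89, ignoring clustering). Comparing them by eye is therefore not a test.

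**The case against.** **The limitation is disclosed.** The Design section says that approach is not a separate factor, says why, and words the first route as approach together with tool. This stands, and it makes the correction largely one of labelling. It does not remove the problem: the same section goes on to count the contrast towards a targeted-universal comparison, and the sample-size statement carries no such caveat.

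**Neither route works.** A reader might infer this, but the documents do not support it. The second route in Design identifies factors associated with a positive screen inside the universal arms, where the tool can be held fixed. For yield, the nested contrast of everyone against linked presentations only is the natural policy question. There the (1−f) factor is part of the quantity of interest, not a bias.

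**The error bars are wrong.** A reader might infer this from the overlap. If the two groups were compared as independent samples, the standard error would be too large by √((1+f)/(1−f)): 1.22, 1.53 and 2.00 times for f = 0.2, 0.4 and 0.6, ignoring clustering. But no such two-sample test is stated; the simplest reading of Planned analysis is an intervention effect in each population. Such a test would in any case be conservative.

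**The simulation adds nothing.** This is not shown either. Its method is not described, and such detail may properly sit in an analysis plan that is not at hand.

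**An interaction analysis is already planned.** Planned analysis foresees multilevel modelling of interactions and interaction analysis of patient characteristics. The term needed here is therefore close to what is intended, but it is not named as the test of approach.

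**Screening approach is not what the trial is powered for.** This is right. None of the five hypotheses tests targeted against universal screening, and in the Study aim the two approaches describe how patients are found.

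**Conclusion.** The point holds for the randomised contrast. Three targeted AEDs against six universal ones is a comparison of packages, tool plus approach, and the approach effect has no degrees of freedom once tool is in the model. This follows from the Synopsis and Table 1 and needs no assumed figure. The statement that the sample size accounts for screening approach has no basis in the calculation given.

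The route inside the universal AEDs can inform approach, as a non-randomised comparison limited to FAST and M-SASQ. The intention-to-treat analysis on both groups does not, by itself, test whether the intervention effect depends on approach. The percentages in the working rest on assumed linked shares and positivity rates and serve only as illustration.

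The primary intervention comparison is not affected, because each intervention arm contains exactly one SIPS-PAT AED. This is a should-fix.

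A related inconsistency: the description of the Brief Lifestyle condition has its staff trained in universal screening, while Table 1 places one SIPS-PAT AED there. These passages must be reconciled. Read literally, that one AED would break the aliasing, but a contrast resting on a single department could not separate approach from that department's own level.

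**What to change.** - **Synopsis and Design:** describe SIPS-PAT v FAST or M-SASQ as a comparison of packages (tool plus approach), and do not count it as a comparison of approach alone.
- **Sample size calculation:** remove the statement that the calculation covers screening approach.
- **Approach, screening yield:** base the conclusion on the six FAST and M-SASQ AEDs, within each tool and labelled non-randomised. Report patients screened and cases found if all attenders are screened v linked presentations only, with the overlap handled in the standard errors. State that linked-presentation status is recorded for screen-negative patients too, since the yield figures depend on it.
- **Approach, patient outcomes:** in Planned analysis, replace the separate analyses of overlapping groups with one model that contains an intervention by linked-presentation term and accounts for AED.

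The cost is protocol wording and one model term. No sites or patients are added, provided linked status is captured for everyone screened. The downside is that the approach conclusion is limited to two tools in six AEDs. For outcomes it rests on about 882·6/9 = 588 patients followed up at 6 months, on the protocol's own expectation, and it cannot speak to staff uptake under targeted screening.
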